### MIRO study phone app

The MIRO app (developed by KeyLead Health) will be used to collect all patient-reported outcomes, from which they will be automatically integrated into the clinical database. This app is customised to track and process participants’ trial-related activities in real time. Patient’s confidentiality is protected by adherence to the Australian Privacy Principles established by the Privacy Act 1988. The data platform has Protected Certification from The Australian Signals Directorate and is Health Insurance Portability and Accountability Act compliant. Data are encrypted using the Advanced Encryption Standard with a 256-bit key standard at rest and with Transport Layer Security/Secure Sockets Layer at transit.

### Data monitoring

The audit plan will involve 100% manual verification checks on a 10% random sample of participant files.

### Safety monitoring for patients

Medication or procedure-related adverse events will be monitored during the procedures and at each subsequent visit, with details of the event recorded on the electronic case report form using standard terminology as per the Common Terminology for Adverse Events (V .5.0). A safety monitoring committee will review all cases and adverse events which occur within the context of this cohort. The safety monitoring committee will convene at least weekly to review all patients’ safety and at the time of an adverse event.

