### Objective

This study aims to investigate the efficacy and safety of FMT in inducing and maintaining remission in Crohn’s disease.

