### Primary and secondary endpoints

The primary and secondary endpoints are detailed in table 1.

**Table 1 T1:** Primary and secondary endpoints

Outcome	Definition	Timepoint
Primary		
Clinical response	CDAI decrease of ≥100 or CDAI<150	Week 8
Secondary		
Clinical remission	CDAI<150	Week 8 and week 52Week 16 and week 60 (for open FMT group)
Endoscopic response	SES-CD reduction by 25% and 50%	Week 8 and 52Week 16 and 60
Endoscopic remission	SES-CD ≤2 or absence of ulcers	Week 8 and week 52Week 16 and 60
Histological remission	The absence of ulcers; the absence of acute inflammation histologically; one of either Geboes Score or Robarts Histology Index	Week 8 and 52Week 16 and 60
Radiological remission	IUS (BWT<3 mm and/or Limberg 0 or 1) or MRI (wall thickness<4 mm and no or minimal wall enhancement)	Week 8 and 52Week 16 and 60
Biochemical response	Normalisation of CRP and faecal calprotectin (<50 µg/g, <100 µg/g, <150 µg/g, <200 µg/g, <250 µg/g	Week 8 and 52Week 16 and 60
Time to outcomes	Time taken to achieve clinical response or remission during induction and maintenance phases	Duration of trial
Maintenance of clinical remission	CDAI <150	Weeks 52 or 60
Sustained clinical remission	CDAI <150	Weeks 52 or 60
Steroid-free clinical remission		Weeks 52 or 60
Safety outcomes	Adverse events	Duration of trial
Scientific outcomes	Comparison of genetic, microbiological, metabolic and immunological factors in the responders with the non-responders	Week 8 and 52Week 16 and 60

BWT, bowel wall thickness; CDAI, Crohn’s Disease Activity Index; CRP, C reactive protein; FMT, faecal microbiota transplantation; IUS, intestinal ultrasound; SES-CD, simplified endoscopic activity score for Crohn's disease.

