### Induction phase

Patients assigned to receive upper gastrointestinal delivery of FMT will undergo endoscopic administration of FMT or placebo into the distal duodenum or jejunum at weeks 0, 2 and 6.

Patients receiving lower gastrointestinal delivery will undergo endoscopic administration of FMT or placebo into the ileum or right colon at week 0, followed by weekly FMT or placebo enemas until week 8.

At the week 8 assessment table 2, patients achieving a clinical response to FMT (CDAI decrease of ≥100 points or CDAI <150) enter the maintenance phase. Patients who achieve a partial response to FMT (CDAI decrease of <100 and >70 points) will be offered open-label extension of FMT for a further 8 weeks; if they fail to achieve complete clinical response to FMT at week 16, they will exit the study. Patients receiving initial (induction) placebo will be offered 8 weeks of open-label induction active FMT therapy; if they fail to achieve complete clinical response to FMT at week 16, they will exit the study. Patients receiving placebo therapy who achieve a clinical response at week 8 will exit the study.

**Table 2 T2:** Clinical outcomes assessments

	Method of assessment	Timepoints
Disease activity	Crohn’s Disease Activity Index	Weeks 0, 2, 6, 8 (±16), 16 (or 24), 24 (or 32), 32 (or 40), 40 (or 48), 48 (or 56), 52 (or 60)
Biomarkers	Blood: C-reactive protein	Weeks 0, 2, 6, 8 (±16), 16 (or 24), 24 (or 32), 32 (or 40), 40 (or 48), 48 (or 56), 52 (or 60)
	Stool: calprotectin	Weeks 0, 2, 8 (±16), 24 (or 32), 52 (or 60)
Sonographic assessment	IUS BWT <3 mm and/or Limberg Score 0 or 1; MRI BWT <4 mm and no/minimal wall enhancement	Weeks −3, 8 (±16), 52 (or 60)
Quality of life measures	Short-IBD-Q and EuroQol (EQ5D)	Weeks −3, 8 (±16), 52 (or 60)
Psychological assessment	Hospital Anxiety and Depression Scale (HADS)	Weeks −3, 8 (±16), 52 (or 60)
Endoscopy assessment	SES-CD	Weeks 0, 8 (±16), 52 (or 60)
Histological assessment	Presence of acute inflammation; Robarts Histology Index	Weeks 0, 8 (±16), 52 (or 60)
Diet tolerability	24-hour diet recall; Diet compliance assessment; Food additive survey	Weeks −3, 0, 8 (±16), 52 (or 60)
Safety	Surveillance	Duration of trial and up to 5 years following withdrawal/exit

BWT, bowel wall thickness; SES-CD, simplified endoscopic activity score for Crohn's disease.

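### The adverse event recording rule covers medication- or procedure-related events, while the safety outcome and the committee's remit cover all adverse events

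*Protocol article*

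**What the plan says.** The article gives one rule for recording adverse events, under the heading on safety monitoring for patients. It states that "Medication or procedure-related adverse events will be monitored during the procedures and at each subsequent visit". The same sentence sends the particulars of those events to the eCRF, coded in a standard vocabulary. Its subject carries a relatedness qualifier, and the article does not define what counts as related.

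Three other places describe safety without that qualifier:

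- The following sentence of the same section: "A safety monitoring committee will review all cases and adverse events which occur within the context of this cohort". The committee is to "convene at least weekly to review all patients’ safety and at the time of an adverse event".
- The safety row of Table 1 (primary and secondary endpoints): "Safety outcomes Adverse events Duration of trial".
- The safety row of Table 2 (clinical outcomes assessments), where surveillance runs for "Duration of trial and up to 5 years following withdrawal/exit".

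Safety is also half of the stated objective: "This study aims to investigate the efficacy and safety of FMT in inducing and maintaining remission in Crohn’s disease".

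**The concern.** Randomisation allows the arms to be compared on all events without deciding what caused each one. If causality is judged before an event reaches the eCRF, part of that advantage is lost, and an event that was not recorded cannot be restored at analysis.

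Attribution is hard in this trial. Patients stay on stable background Crohn's therapy, including immunomodulators and biologics. All of them take three antibiotics before randomisation. Maintenance doses are 4 or 8 weeks apart, depending on route. A site could reasonably attribute a chest or bloodstream infection to a background drug, or fail to link a late event to a dose given weeks before. Under the literal rule, such an event would not have to be recorded.

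At stake is whether the safety comparison that the trial reports is the one that Table 1 defines.

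**Working it through.** The article states no adverse event rate, no expected share of related events and no safety power, so there is no figure to reproduce. The check is a reading of the text, followed by a small piece of algebra on what a filter could do.

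**Step 1: the statements side by side.**

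1. Recorded on the eCRF (safety monitoring, first sentence): medication- or procedure-related events.
2. Reviewed by the committee (safety monitoring, second sentence): all cases and all adverse events.
3. Analysed as the safety outcome (Table 1): adverse events, unrestricted.
4. Surveillance (Table 2): safety during the trial and for up to 5 years after exit, unrestricted.

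Items 2 to 4 agree with each other. Item 1 is narrower, and it is the only one that says what goes on the eCRF. The article names no other route by which an event judged unrelated would reach the committee or the analysis.

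**Step 2: is the gap filled elsewhere?**

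- Crohn's worsening: largely yes. CDAI, CRP and calprotectin are measured at scheduled visits (Table 2). The section on early discontinuation counts clinical recurrence as treatment failure and asks for a disease activity assessment at withdrawal. These are efficacy or withdrawal data, not adverse event records.
- Serious events: in part. The same section lists serious events that force therapy to stop, with no relatedness limit. It is a withdrawal criterion, not a recording rule, and it does not reach serious events after which therapy continues.
- Infections and other events attributed to background treatment: the article offers no substitute.

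**Step 3: what a filter would do to the comparison.** Assume one event per patient. Let *b* be the background proportion with an event in each arm and *e* the excess in the FMT arm. Let s_F and s_P be the shares of background events judged related in the FMT and placebo arms, and s_e the share of the excess judged related.

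- All events recorded: (b + e) − b = e.
- Related events recorded: (s_F·b + s_e·e) − s_P·b = s_e·e + (s_F − s_P)·b.

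If attribution is blind, s_F and s_P should be about equal. The recorded difference is then s_e·e, which cannot exceed e and is zero when e is zero. The filter then loses events and can shrink a real excess, but it does not create one. If allocation is known, s_F and s_P may differ, and the second term can add or hide a difference of either sign.

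**Step 4: where each case applies.** The section on double blinding covers participants, clinicians, the research team and assessors, so the equal-share case is the natural one for the randomised phases. Open-label FMT is given with allocation known. The statistical analysis section compares blinded and unblinded FMT combined against placebo. It does not say which outcomes this covers; if safety is among them, the unequal-share case applies there.

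**Step 5: size.** None of b, e, s_F, s_P or s_e is in the document. Nor can the effect on power be signed in general. Removing background events along with some of the excess can lower power, but it can raise power if the excess is kept more often than the background. No single figure would be a fair summary.

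**The case against.** The strongest reply is that the first sentence describes checks around procedures and at visits and was not meant to limit collection. A committee that meets at least weekly and reviews every adverse event needs those events to be captured, and Table 1 is unrestricted. The article also condenses a fuller protocol (version 1.4) and cites good clinical practice and national safety reporting guidance, so definitions, causality assessment and the collection window may well be set out there.

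Much of this stands. It may be what was intended, and it rules out several stronger readings that a reader might infer:

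- **That unrelated events are definitely not recorded, or that the committee can never see them.** The article does not say so, and the committee's stated remit points the other way.
- **That Crohn's worsening disappears from the trial.** It is collected through activity scores, biomarkers and treatment failure.
- **That attribution will favour one arm in the randomised phases.** It is made under blinding. The placebo has no odourant, which might weaken the blind, but nothing in the document connects this to causality judgements.
- **That a given loss of power follows.** That needs rates and shares that the document does not supply.

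What the reply does not remove is the wording. This is not a detail left to another document. The article states a recording rule, the rule carries a restriction, and the restriction disagrees with the endpoint that it feeds.

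**Conclusion.** The point holds as an inconsistency between the eCRF recording rule on one side and Table 1 and the committee's remit on the other. If the rule is followed as written, the main consequence in the blinded phases is an incomplete safety comparison. Biased attribution is a more serious possibility where open-label FMT enters the pooled comparison with placebo.

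The size cannot be stated. The conclusion rests on reading the recording sentence literally and on the full protocol not setting a broader rule; neither can be confirmed from the article. Confidence is therefore moderate. The text conflict is plain, but what sites actually record is not known. The correction is worth making because safety is a stated objective and events lost at collection cannot be recovered.

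**What to change.** Reconcile the first sentence of the safety monitoring section with the committee's remit and Table 1. Suggested content: all adverse events are recorded on the eCRF regardless of suspected cause, and relatedness is entered as a separate field. Compare all adverse events between arms as the safety outcome, and report related events additionally.

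Check the full protocol and the eCRF instructions first. If they already require all events, only the article's sentence needs correcting.

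The cost is a wording change, possibly one eCRF field, and a little more data entry for minor unrelated events. No extra visits or patients are needed.

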### Patient involvement

Patients were not involved in the design and conduct of this research.

### Statistical analysis

Primary analysis will be using modified intention-to-treat population, that is all patients who were randomised and received at least one dose of the study treatment. Per-protocol analysis will be performed as a secondary analysis.

The primary endpoint is the achievement of clinical response at week 8, defined as either a reduction in CDAI of ≥100 points or a CDAI score of <150 points. This primary outcome will be analysed using a general linear model with binomial distribution and log link, with results presented as risk ratio and 95% CIs. A two-sided p value of less than 0.05 will be considered statistically significant.

All binary secondary outcomes in both the induction and maintenance phases will be compared between arms using a general linear model with binomial distribution and log link. Time taken to achieve a clinical outcome will be compared between groups using Kaplan-Meier survival analysis and Cox regression model.

All continuous secondary outcomes will be compared between groups using analysis of covariance. Model fit will be assessed by visual inspection of the residuals, and outcomes might be transformed if required. If the transformation will not yield improved model fit, then the rank sum test will be used for comparison.

There will not be corrections for multiple comparisons, but the results will be interpreted in view of multiple comparisons.

The number of participants in the open-label phase extension is expected to be small, providing for mainly descriptive analysis. However, to gain a larger impression of the impact of active FMT versus placebo, combined active blinded and unblinded FMT outcomes compared with placebo will be assessed.

The primary aim of the open-label induction phase is to enable the majority of participants in the study to access FMT therapy.

Subgroup analyses will include outcomes in the upper and lower gut delivery cohorts, as well as many of the patient demographic variables.

No interim analyses will be performed. The missing data strategy will depend on the type of intercurrent event.

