**Trial registration number:**

ClinicalTrials.gov: NCT04970446; Registered on 20 July 2021.

STRENGTHS AND LIMITATIONS OF THIS STUDYThis is a randomised placebo-controlled study, providing the highest level of evidence about both efficacy and safety of faecal microbiota transplantation (FMT) in Crohn’s disease for the induction and maintenance of remission.The optimisation phase of diet and antibiotics is postulated to enhance FMT engraftment.The scientific analyses will determine organisms, and metabolic pathways, associated with response or lack of response to FMT.Confining the study to two tertiary centres will ensure robust compliance with the study protocol, while the diverse patient population ensures generalisability.The use of the Crohn’s Disease Activity Index as the primary endpoint, while providing a standard means for establishing comparability with other studies, is inherently largely subjective and therefore potentially unreliable.

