Studies evaluating FMT in UC have demonstrated associations between specific organisms in donor FMT and the extent of engraftment with therapeutic response.^9 18 44^ A limitation of the current scientific literature is the variability in culturing and sequencing techniques and depth of sequencing capabilities. A recent advancement in combining genome and culture techniques has facilitated enhanced metagenomic sequencing, improving taxonomic classification down to subspecies level.^45 46^ This study will use this technology to help establish the mechanism of action of FMT in Crohn’s disease and define the microbial and associated metabolic factors central to Crohn’s disease pathogenesis and treatment response. Identifying specific bacterial factors associated with FMT therapeutic benefit and failure will lead to a more sophisticated approach to the development of microbial therapeutics in IBD and a more personalised approach to treating Crohn’s disease.

The MIRO study will define the therapeutic value of FMT in Crohn’s disease. The study design, a large randomised double-blind placebo-controlled trial, aims to definitively establish this proof of concept.

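### The no-correction rule exempts no endpoint, so as written it also covers the sequencing-based scientific outcomes, where a large share of the reported associations could be false

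*Protocol article*

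**What the plan says.** The multiplicity rule is one sentence in the Statistical analysis section: "There will not be corrections for multiple comparisons, but the results will be interpreted in view of multiple comparisons". It follows the methods for the primary, binary secondary, time-to-event and continuous secondary outcomes, and it makes no exception. The only significance threshold in the section is in the paragraph on the primary endpoint: "A two-sided p value of less than 0.05 will be considered statistically significant".

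Table 1 places the scientific outcomes under the secondary endpoints and defines them as: "Comparison of genetic, microbiological, metabolic and immunological factors in the responders with the non-responders". They are assessed at weeks 8 and 52, or 16 and 60.

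Two other places show what these analyses are for. The strengths and limitations box says: "The scientific analyses will determine organisms, and metabolic pathways, associated with response or lack of response to FMT". The Discussion describes sequencing methods as "improving taxonomic classification down to subspecies level", says the study will use this technology, and then states: "Identifying specific bacterial factors associated with FMT therapeutic benefit and failure will lead to a more sophisticated approach to the development of microbial therapeutics".

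**The concern.** For about a dozen clinical endpoints, leaving p-values unadjusted and asking the reader to make allowance is a defensible choice. The scientific outcomes are a different kind of analysis: four families of factors, at least one of them measured by fine-resolution sequencing, screened for association with response at more than one timepoint. A promise to interpret with multiplicity in mind sets no threshold, procedure or reporting rule. It gives a reader no way to tell which named organism is a chance finding.

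The analysis is also not presented as hypothesis-generating. The article expects it to settle which organisms and pathways go with response and to feed the development of treatments. That claim is stronger than the error control behind it. At stake is the reliability of the mechanistic results; the primary efficacy comparison is not affected.

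**Working it through.** **1. The plan's own figure.** The article gives no number for multiplicity, but the sample size fixes how many patients the comparison can draw on. Inputs (Sample size, Randomisation and stratification, Discussion): 30% v 60% response, two-sided 0.05, 80% power, 2:1 allocation, 20% dropout. The pooled proportion is (0.3 + 2 × 0.6)/3 = 0.5. Controls needed:

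[1.96 × √(1.5 × 0.25) + 0.842 × √(0.3 × 0.7 + 0.6 × 0.4/2)]² / 0.3² = (1.200 + 0.484)² / 0.09 ≈ 31.5, rounded up to 32.

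With 64 on FMT the total is 96, and 96/0.8 = 120. The stated 96 and 120 are reproduced.

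**2. Size of the comparison (assumed).** Table 1 does not say which patients enter it. Taking the 64 FMT completers at the planned 60% response gives 64 × 0.6 ≈ 38 responders and 26 non-responders.

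**3. Chance hits if nothing is associated.** Expected number = features × 0.05. The feature count is not in the article, so a range is assumed:

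- 200 features: 10
- 1000 features: 50
- 5000 features: 250

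**4. False share of the hits.** With a share t of features truly associated and power w for each,

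false share = 0.05(1 − t) / [0.05(1 − t) + t·w].

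This does not depend on the number of features. For a two-sample t-test with 38 v 26, w is 64% for a difference of 0.6 SD and 87% for 0.8 SD.

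| Truly associated | False share, w = 64% | False share, w = 87% |
|---|---|---|
| 2% | 0.049/(0.049 + 0.0128) = 79% | 0.049/(0.049 + 0.0174) = 74% |
| 5% | 0.0475/(0.0475 + 0.032) = 60% | 0.0475/(0.0475 + 0.0435) = 52% |
| 10% | 0.045/(0.045 + 0.064) = 41% | 0.045/(0.045 + 0.087) = 34% |
| 20% | 0.04/(0.04 + 0.128) = 24% | 0.04/(0.04 + 0.174) = 19% |

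Hits are mostly false when t is below 0.05/(0.05 + w): about 7% at w = 64% and about 5% at w = 87%.

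**5. What control of the false discovery rate would do.** Simulation with 1000 independent features, 5% truly different by 0.8 SD, 38 v 26: uncorrected testing gives about 48 false and 44 true hits. Benjamini-Hochberg at 10% holds the false share to about 10% and keeps about 26 true hits. With 2% truly different, it keeps about 8 of about 17 (0.87 × 20) true hits. If those 2% differ by only 0.6 SD, it keeps fewer than 2 of about 13, but uncorrected those 13 would sit among about 49 false ones.

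Bonferroni would be harsher. At 1000 features it needs p < 0.00005, and power for a 0.5 SD difference falls from about 50% to about 2%.

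**The case against.** The strongest reply concerns scope. The no-correction sentence follows paragraphs about treatment comparisons; for instance, "All binary secondary outcomes in both the induction and maintenance phases will be compared between arms". The scientific outcomes are a different contrast, and the section names no test, model or threshold for them. The article condenses a fuller protocol, and a separate analysis plan may exist; bioinformatic detail is commonly left to such documents.

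Part of this stands. The absence of a named test or a feature count is not a fault in an article. But multiplicity is not left open here: the article decides it, in a sentence with no exception, and Table 1 puts the scientific outcomes among the endpoints that the sentence covers. If an unseen plan does control the false discovery rate, it conflicts with this sentence and the two need reconciling.

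A reader might go further and infer that the plan tests hundreds or thousands of features, each at 0.05, so that the resulting list must be mainly chance. The documents do not support that. Sequencing resolution is not a count of tests. The 0.05 threshold is stated for the primary outcome, and applying it to each feature is an inference. Whether most hits are false depends on how sparse the true associations are: at 10% truly associated and the same power, false hits are a minority. The 38 v 26 split is also only one reading, since patients given open-label FMT could enlarge the sample.

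**Conclusion.** The concern holds in a conditional form. As written, the no-correction rule reaches the scientific outcomes, and the commitment to cautious interpretation puts no procedure in its place. How many hits would be false cannot be read from the article. Under the assumptions shown (per-feature testing at 0.05, 38 v 26 patients, 64–87% power), the false share is about 52–79% if 2–5% of features are truly associated and about 34–41% if 10% are. A large share of the named associations, and possibly most, could therefore be false, with no label to tell the reader which. The article gives no basis for choosing among these sparsity levels, so nothing firmer than that can be claimed. The primary endpoint, the 96/120 sample size and the clinical secondary endpoints are unaffected. The change should be made, but the main result does not depend on it.

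**What to change.** Limit the no-correction sentence to the clinical endpoints and add a rule for the scientific outcomes, for example:

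*For the scientific outcomes, the false discovery rate will be controlled within each family (microbiological, metabolic, genetic, immunological) and timepoint by the Benjamini-Hochberg procedure at a pre-specified level. q-values will be reported. Only features that pass will be described as associated with response; all others will be labelled exploratory.*

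A level of 5% or 10% is reasonable; what matters is fixing it in advance. If the full protocol or analysis plan already has such a rule, the published sentence should be brought into line with it.

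The cost is one sentence and a line of code. The real price is a shorter list of named features and the loss of some true ones, which may be severe if the associations are both rare and modest.

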**Methods and analysis:**

At two specialist inflammatory bowel disease centres, 120 enrolled patients will have a 3-week period of diet optimisation (removal of ultra-processed foods) together with a 7-day course of antibiotics (to facilitate subsequent FMT engraftment). Patients will then be stratified to upper gut (for disease proximal to the splenic flexure) or lower gut (distal to the splenic flexure) disease. Patients will then be randomised in a 2:1 ratio to receive anaerobically prepared stool or placebo for 8 weeks either by gastroscopy, or colonoscopy and enemas. Clinical response at 8 weeks (Crohn’s Disease Activity Index (CDAI) reduction ≥100 points or to <150 points) is the primary outcome measure. Non-responders to placebo and partial responders to FMT (CDAI decrease <100 but >70) receive FMT for weeks 8–16.

Patients achieving clinical response from FMT after 8 or 16 weeks will be randomised in a 1:1 ratio to either a 44-week maintenance phase of FMT or placebo. Patients will receive FMT from one donor throughout the study.

The MIRO study will establish whether FMT is an effective and safe therapy to induce and maintain remission in patients with active Crohn’s disease.

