### Randomisation and stratification

Eligible patients will be stratified according to their historical maximal extent of intestinal involvement. Patients with intestinal disease proximal to the splenic flexure will be assigned upper gastrointestinal delivery of therapy. Patients with disease distal to the splenic flexure, or an ileorectal or ileosigmoid anastomosis, will receive lower gastrointestinal delivery.

There will be a total of four randomisation tables. Each table will represent stratification according to the assignment to upper or lower gastrointestinal delivery, and the phases of the study (induction or maintenance). Randomisation within these tables is computer generated by a statistician and then uploaded to a web-based platform.

For the induction phase, patients are randomised to FMT therapy or placebo in fixed block sizes of three patients in a ratio of 2:1, respectively. Re-randomisation occurs for participants entering the maintenance phase, from either the induction or open-label extension phases, in blocks of two in a ratio of 1:1.

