## Discussion

Despite the recognised central role of the microbiome in Crohn’s disease pathogenesis, no large-scale placebo-controlled trials have been conducted to date examining FMT for this indication. FMT is an established treatment option for patients with recurrent *Clostridioides difficile* infection, and more recently as an effective therapy for the induction and maintenance of remission in patients with UC. Many FMT studies have been performed for other gastrointestinal indications; however, no universal guidelines exist to direct use of FMT with regard to mode of administration, dose or treatment intervals.

The MIRO study protocol has been designed to best examine the efficacy of FMT in Crohn’s disease.

The sample size calculation is based on an alpha value of 0.05 (two sided), power of 80%, an expected rate of the primary outcome of 60% in the intervention arm and 30% in the comparator arm. Allowing for a dropout rate of 20%, a total of 120 patients will be required to achieve a non-dropout number of 96 patients completing the induction phase of the study.

The allocation of donors to patients will be at least eight patients for each donor, to enable the identification of donor effects. An anaerobic processing technique will be used to best preserve obligate anaerobes, hypothesised to be key organisms in efficacy,^27^ given their reduced abundance in cohorts of patients with Crohn’s disease.^1^ The stool preparation will be in liquid form rather than encapsulated lyophilised stool to maximise the viability of bacterial species. Freezing FMT for storage at −80°C is a practical necessity to enable participants to receive a single donor for the duration of the trial, for transportation between sites, for the screening process of donor stool at a TGA approved Good Manufacturing Practice facility and to allow for the required 3-month quarantine phase prior to retesting. The FMT will be frozen with 10% glycerol at −80°C and thawed for administration. Culture-based viability studies have previously demonstrated minimal impacts on different bacterial groups when freezing faecal material at −80°C.^26^

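### The supplementary comparison of pooled blinded and open-label FMT with placebo is not randomised and cannot support a claim of FMT effect over placebo

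*Protocol article*

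**What the plan says.** The primary analysis is the randomised week-8 comparison of clinical response in the modified intention-to-treat population. For the open-label extension, the Statistical analysis section says "The number of participants in the open-label phase extension is expected to be small" and expects mainly descriptive work. It then makes an exception: to get a broader view of FMT against placebo, "combined active blinded and unblinded FMT outcomes compared with placebo will be assessed". The same section sets the general threshold, "A two-sided p value of less than 0.05 will be considered statistically significant", and declines multiplicity correction.

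Other sections fix who supplies the unblinded outcomes:

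- Abstract: "Non-responders to placebo and partial responders to FMT (CDAI decrease <100 but >70) receive FMT for weeks 8–16".
- Induction phase: "Patients receiving initial (induction) placebo will be offered 8 weeks of open-label induction active FMT therapy". Placebo patients who respond at week 8 leave the study.
- Open-label phase: response at week 16 is judged as change from screening, not from the start of open-label FMT.
- Discussion: patients are unblinded at week 8 so that the extension can take place.

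**The concern.** The pooled FMT group differs from the placebo group in ways that randomisation does not balance.

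1. Placebo non-responders can appear on both sides, as placebo failures at week 8 and as FMT patients at week 16.
2. Entry to the pool depends on the assigned arm and on the week-8 outcome.
3. FMT partial responders get a second course. Placebo patients with the same partial response get no second placebo course and stay failures.
4. Unblinded week-16 outcomes are set against blinded week-8 outcomes, on an index that the article's own limitations statement calls largely subjective. No placebo induction group remains at week 16.
5. Scoring from screening carries earlier improvement forward. A placebo patient who had fallen 80 points by week 8 needs only 100 − 80 = 20 more to count as an FMT response.

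The stake is a result that looks like added evidence of efficacy but mixes any FMT effect with selection, time, diet and knowledge of treatment.

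**Working it through.** **Plan's own figure.** Inputs: "power of 80%, an expected rate of the primary outcome of 60% in the intervention arm and 30% in the comparator arm"; two-sided alpha 0.05; "patients are randomised to FMT therapy or placebo in fixed block sizes of three patients in a ratio of 2:1, respectively". With pooled proportion (0.3 + 2 × 0.6)/3 = 0.5, the placebo arm needs

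[1.96 × √(1.5 × 0.5 × 0.5) + 0.8416 × √(0.3 × 0.7 + 0.6 × 0.4/2)]² / 0.3² = (1.200 + 0.483)² / 0.09 ≈ 31.5, so 32.

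That gives 32 + 64 = 96, and 96/0.8 = 120. This agrees with "a total of 120 patients will be required to achieve a non-dropout number of 96 patients completing the induction phase of the study". Power at 64 v 32 is 80.6%. The sample size is not in dispute.

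**Size of the reused group.** At 30% placebo response, non-responders number 0.7 × 32 = 22.4 among completers, or 0.7 × 40 = 28 if all 120 are counted. Against 64 FMT completers they are 22.4/(64 + 22.4) = 26% of the pooled FMT patients, before any second courses are counted.

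**Two ways to count.** The article does not choose between them. The numerator in both is FMT week-8 responders + converted FMT partial responders + converted placebo non-responders.

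- Each patient once: divide by FMT patients + placebo non-responders.
- Each FMT course: also add the FMT partial responders to the denominator.

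**Direction, with no FMT effect.** Assumptions not in the article: CDAI-change SD 90; 30% week-8 response in both arms; 64 v 32. Partial responders then make up about 12.4% of the FMT arm, or about 8 patients.

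| Setting | Week-8 FMT responders | Converted partials | Converted placebo | Each patient once | Each course |
|---|---|---|---|---|---|
| No drift, week 8/16 correlation 0.7 | 0.30 × 64 = 19.2 | 0.351 × 8.0 = 2.8 | 0.156 × 22.4 = 3.5 | 25.5/86.4 = 29.5% | 25.5/94.4 = 27% |
| 60-point drift, correlation 0 | 19.2 | 0.556 × 8.0 = 4.4 | 0.557 × 22.4 = 12.5 | 36.1/86.4 = 41.8% | 36.1/94.4 = 38.3% |

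Placebo is 30% in both rows, so the pooled rate can fall on either side of it. The second chance for partial responders, taken alone, moves the FMT arm up even without drift: (19.2 + 2.8)/64 = 34.4% in the first setting.

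**Rejection by a naive two-sided 5% test, with no FMT effect.** Assumptions: change from screening with mean −60 and SD 75 (about 30% week-8 response), correlation 0.3–0.6, arms of 80/40 or 64/32.

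| Assumed non-specific fall by week 16 | Each course | Each patient once |
|---|---|---|
| 0 points | about 4–6% | about 4–6% |
| 60 points | about 14–19% | about 26–33% |

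The SD-90 set (correlation 0–0.7, drift 0, 30 or 60 points, 64/32) gives 4.5–13.5% by course and 4.3–22.4% by patient. In that set the randomised week-8 comparison alone stays at 4.7–5.2%.

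**The case against.** The strongest reply is that this is a minor, non-confirmatory sentence. The pooled comparison is not an endpoint in Table 1 and plays no part in the sample size. It follows a remark that the open-label work is mainly descriptive. The sentence names no model, p-value, time point or counting rule, and an SAP may say how repeated patients are handled. The simulated inflation comes from an assumed drift for which the article gives no figure; with no drift, rejection is close to nominal. The reused group could also be smaller than 22 to 28, because open-label FMT is only offered.

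Much of this stands, and it rules out three stronger readings that a reader might infer:

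- *That the plan commits to an invalid significance test.* It plans a comparison with placebo. The 0.05 threshold is given with the primary outcome and is not tied to this contrast.
- *That the bias must favour FMT.* Selecting placebo failures works against FMT, while the second course, time and unblinding work for it.
- *That the primary result is compromised.* The randomised week-8 analysis does not use the open-label data.

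What does not stand is the defence that this is only missing detail. The contrast is stated as an exception to the descriptive analysis, with the aim of judging FMT against placebo. A model for repeated patients would repair the variance. It would not repair the selection, the unblinding, the unequal number of courses or the absent week-16 control.

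**Conclusion.** The concern holds for a supplementary analysis; severity is moderate. The flaw follows from the protocol's own crossover rules and needs no numerical assumption: the pooled contrast is not randomised and cannot support a claim that FMT works better than placebo. Its size is uncertain. The rejection rates depend on the assumed CDAI distribution, correlation, drift and counting rule, so they are illustrative ranges and not predictions for this trial. The count of 22 to 28 reused placebo patients rests on the planned 30% response and on full uptake of the open-label offer. Whether that is small is a matter of judgement, but it is up to 70% of the placebo arm.

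**What to change.** Drop the pooled FMT-versus-placebo contrast from the Statistical analysis section. At minimum, label it descriptive, with no p-value and no efficacy claim. State that inference on FMT versus placebo for induction rests only on the randomised, blinded week-8 comparison. Report open-label week-16 results as single-arm proportions with exact confidence intervals, separately for placebo crossovers and FMT partial responders, and add the within-patient change from week 8 to week 16 so that improvement before open-label FMT is not credited to it.

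The cost is one sentence of the analysis section. No visit, data item or sample size changes, and no valid evidence is lost.
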